## Abstract

**Background:**

The physical activity (PA) levels of many children and adolescents in Australia are currently insufficient to promote health benefits. Physical education (PE) programs aim to promote PA and reach nearly all school-aged children, but PA levels within PE lessons are often low. PE teachers may influence children’s motivation to be physically active in PE lessons, but little is known about teacher strategies that effectively motivate children to participate in PA, and few intervention studies have examined motivational strategies in PE. The purpose of this study was to compare the effect of three motivational strategies, each based on Self-Determination Theory (SDT), on PA levels, and their hypothesized antecedents, during year 8 PE lessons.

**Methods/design:**

This study employed a cluster-randomized controlled trial design. Following a familiarization session, PA levels and hypothesized PA antecedents were measured during a baseline lesson and a post-intervention or control lesson. Teachers (n = 16) and their classes from five secondary schools in Sydney, Australia were randomly assigned into four blocks and instructed to provide one of four 20-min lesson teaching strategy conditions: (1) explaining the relevance of activities; (2) providing choice from PA options selected by the teacher; (3) providing equipment and free choice of activities; or (4) usual practice. The primary outcomes were lesson time spent in moderate-to-vigorous PA, and motivation towards the lesson. Secondary outcomes were perceptions of teacher behavior, psychological needs satisfaction, and lesson time spent in sedentary behavior. PA and sedentary behavior were measured during baseline and post-intervention lessons with waist-mounted Actigraph GT3X accelerometers. Teacher behavior, psychological needs satisfaction, and motivation were assessed via questionnaires at the end of each lesson. Linear mixed-model analyses will be run on all outcomes, with students nested within teachers as a random effect.

**Discussion:**

Study findings will inform the development of effective SDT-based teaching strategy interventions to enhance students’ psychological needs satisfaction, motivation, and PA levels. More effective teaching strategies may be identified that are capable of improving adolescents’ PA levels, and thereby provide beneficial population health outcomes.

**Trial registration:**

This trial is registered with Current Controlled Trials and is traceable as ISRCTN07038258.

## Background

Physical inactivity is one of the leading modifiable causes of death and disease in Australia [1]. Regular physical activity (PA) decreases the risk of developing cardiovascular disease, diabetes, some cancers, obesity, osteoporosis, and other chronic conditions [2], but many children and adolescents in Australia are not sufficiently active to accrue associated health benefits [3]. In response to this evidence and data showing rising levels of childhood and adolescent obesity [3], public health efforts have emphasized the importance of schools in the promotion of PA among youth [4-8].

Recently, the Australian Government-commissioned Crawford Report [9] described the central role of physical education (PE) programs for increasing the PA levels of youth. PE lessons reach the majority of school-aged youth, and therefore the promotion of PA through PE has far-reaching health implications for millions of Australian youth [9]. Students’ PA levels in PE lessons, however, are often very low [10]. To achieve increased PA both within and beyond PE lessons, it is important for school-aged youth to be sufficiently and appropriately motivated [11,12]. PE teachers can play an important role in motivating students to be physically active within [13], and beyond PE lessons [14]. Youth who lack motivation in PE often report negative experiences and relationships with their PE teachers [15], which is why it is imperative for researchers to examine teaching strategies for PE teachers to motivate their students more effectively toward achievement of higher levels of PA.

### Theoretical framework

The current study is based on Self-Determination Theory (SDT) [16,17] which has been widely applied to a variety of life contexts, including education [18], sport [19], exercise [20], and PE [11,21]. According to SDT tenets, social-contextual factors (e.g., teaching strategies used by PE teachers) can affect individuals’ motivation by satisfying (or undermining) three key psychological needs: 1) autonomy: the need to self-endorse activities and beliefs; 2) competence: the need to effectively interact with one’s environment and yield desirable outcomes; and 3) relatedness: the need to feel connected and accepted by significant others [16,17].

In the context of PE, when teachers use motivational strategies that satisfy key psychological needs, students will feel more self-determined to participate in PE, and thus will be more physically active during lessons [11]. Motivational strategies that support student needs include: (1) “choice”: providing students with the opportunity to make decisions about the activities they undertake during lessons; (2) “relevance”: providing a rationale and explaining to students the relevance of an activity; (3) “acknowledgement”: acknowledging students’ difficulties when learning skills; and (4) “feedback”: providing feedback using praise for students’ effort and improvement. Previous studies have shown that these strategies can satisfy the three key psychological needs in the PA context, and are essential to well-being, learning, and the development of autonomous forms of motivation (e.g., intrinsic motivation) [22-24].

In contrast, teachers’ motivational strategies that undermine student autonomy (e.g., controlling strategies such as discouragement of student initiative, overt teacher control, conditional student acceptance and praise) may thwart students’ psychological needs and thereby result in controlling forms of extrinsic motivation or lack of motivation, anxiety, and poor psychological adjustment [25]. In the PE context, such dysfunctional motivational strategies may reduce PA levels. Experimental research in the contexts of education [26] and PA promotion in adults [27] has supported these theoretical predictions and a recent study showed that providing children (aged 8–12) with choice increased physical activity in a laboratory setting [28].

Despite the apparent influential role of teachers’ motivational strategies, intervention studies to enhance teachers’ motivational strategies in PE are rare. Chatzisarantis and Hagger [29] evaluated the effects of an SDT-based PE intervention in which the five teachers in the experimental condition learned the four aforementioned motivational strategies, and five teachers in the comparison condition learned only the “relevance” and “feedback” strategies. Students in the experimental condition, whose teachers had also learned the “choice” and “acknowledgement” strategies, reported greater self-determined motivation toward PE and more leisure time PA than comparison participants. Although these results are encouraging, limitations of the study include: (1) the lack of measurement of PA within the PE lesson and the reliance on self-report PA measures in leisure time; (2) the lack of objective assessment of teacher behaviors leading to an inability to determine to what degree each of the strategies was employed by teachers; and (3) the inability to determine which of the four strategies influenced student motivation. Indeed, Chatzisarantis and Hagger [29] investigated the additive effect of “choice” and “acknowledgement” to “relevance” and “feedback”, but no comparison was made with teachers’ usual teaching style.

In a recent experimental study, Cheon et al. [30] investigated the effect of an SDT-based training program for PE teachers on student motivation and intentions to be physically active outside school. Training involved five hours of multi-media presentations and discussion where teachers learned four types of SDT-based motivational strategies. Compared with controls, students whose teachers had participated in this training reported greater increases in needs satisfaction, self-determined motivation, and intentions to be physically active outside school. Once again, these findings are promising, but the effect of autonomy support on PA during PE lessons was not assessed, and only PA intentions, not actual PA behavior, was measured. Also, Cheon et al. [30] reported that all four types of motivational strategies were implemented by teachers, but the study design did not allow the authors to assess the extent to which each strategy influenced student motivation and other outcomes. Indeed, all teachers learned all four strategies and, thus, it is unknown if some strategies were more effective than others.

In the present study, we addressed a limitation of the Chatzisarantis and Hagger [29] and Cheon et al. [30] studies by employing an objective measure of PA within PE lessons. We also examined the independent effects of different motivational teaching strategies. Specifically, we compared strategies designed to explain relevance and provide choice.

Explaining the relevance of activities and providing opportunities for students to make choices are considered important strategies to promote autonomous student motivation [31]. In academic classrooms, there is evidence that explaining relevance may have a greater impact on student motivation and engagement than providing choice [31,32]. To the authors’ knowledge, no PE-based research has investigated the importance of explaining relevance to students. However, the influence of choice in PE lessons has received some attention. Ward and colleagues [33] investigated the influence of providing adolescent girls with a single choice per PE lesson. They found that this strategy increased self-determined motivation, but did not influence PA levels during PE lessons (as measured by pedometers). It is possible, however, that Ward et al’s [33] decision to only provide one opportunity for choice during a lesson may have minimized treatment effects. Indeed, a meta-analysis [34] found that providing two to four opportunities for choice had the greatest effect on motivation. Lonsdale et al. [11] compared student PA during structured lessons (no choice) and complete free choice periods, during which equipment was provided, but students were able to decide for themselves what activities they undertook. This manipulation resulted in greater PA during the free choice period. Neither Ward et al. [33] nor Lonsdale et al. [11] investigated varying levels of choice or the effect of any other autonomy supportive strategy (e.g., explaining relevance) on students’ need satisfaction, motivation, or PA levels. As noted, no research has investigated the independent effects of these strategies on PA in PE lessons. In the present study, we examined these independent effects by comparing the effectiveness of: (1) “relevance” - explaining the relevance of activities; (2) “providing choice” - providing a number of PA options selected by the teacher; (3) "free choice” – providing complete free choice of activities.

### Aims of the study

The aim of the current project was to investigate the relative effects of three motivational teaching strategies on motivation and PA levels during Year 8 PE lessons. Specifically, we sought to use a cluster-randomized controlled trial to test the effectiveness of three SDT-based motivational teaching strategies, in comparison with usual teaching practices. Understanding which strategies have the greatest impact on PA may allow for the development of effective interventions to increase long-term student motivation and PA during PE lessons, and potentially beyond PE.

There were three main research questions:

Research Question 1: Do students differ across the three motivational teaching strategy conditions and control (usual practice) teaching condition with regard to moderate-to-vigorous PA (MVPA) (primary outcome) and sedentary behavior (secondary outcome) during PE lessons?

Research Question 2: Do student motivation towards PE lessons (primary outcome), needs satisfaction, and perceptions of teacher behavior (secondary outcomes) differ across the three motivational teaching strategy conditions and the control (usual practice) teaching condition?

Research Question 3: Are the effects of motivational teaching strategies on PA and sedentary behavior mediated by teachers’ autonomy supportive behavior and students’ needs satisfaction and motivation during lessons? (See Figure 1).

**Figure 1 F1:**
[figure not shown]
**Hypothesized relationships**
.

### Hypotheses

Compared with usual practice, we hypothesized that PE lessons in which teachers explained the relevance of activities and provided students with choices would:

1. show greater increase in the percentage of time students spend in moderate-to-vigorous physical activity during PE lessons.

2. show greater decrease in the percentage of PE lesson time that students spend in sedentary behavior.

3. show greater increase in students’ autonomous motivation during lessons.

4. show greater decrease in students’ controlled motivation during lessons.

5. show greater increase in students’ perceptions of autonomy, competence, and relatedness during lessons.

6. show greater increase in students’ and independent raters’ perceptions of teachers’ autonomy supportive behavior.

7. produce effects that would be by teachers’ autonomy supportive behavior and students’ needs satisfaction and motivation (see Figure 1).

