## Methods/design

The Human Research Ethics Committee at the University of Western Sydney provided ethical approval for this cluster-randomized controlled trial. The study was conducted in Independent and Catholic schools in Sydney, New South Wales, Australia during 2011. Ten schools were identified using publicly available listings, and invited via telephone and email through publicly available contact details. The first five schools whose principal provided consent were included in the study. Once consent was also received from department heads and teachers of Year 8 PE classes, the research team met briefly with the students to provide basic information about the study. At this time, information sheets and consent forms were distributed to students. Students who were unable to participate in PE classes were not eligible to participate in the study. All other Year 8 PE students who returned signed parental consent forms and provided personal assent were allowed to participate in the study. Students who did not return consent forms still participated in the lessons alongside their peers, but did not wear accelerometers, or complete questionnaires.

Figure 2 provides a summary of the study design, a cluster-randomized controlled trial with four study arms. To begin, a familiarization session was held during a PE lesson. During this lesson, students wore an accelerometer and teachers wore a microphone attached to their shirt that connected wirelessly to an audio recording device. The purpose of this session was to minimize potential reactivity to these monitoring devices during baseline and post-intervention sessions. Data collected during this familiarization lesson will not be analyzed. Baseline and post-intervention data were collected from all participating students, regardless of study arm, during and immediately after two 20-min segments of PE lessons. In between these two lessons, teachers received a brief intervention (three experimental arms) or were asked to continue with usual practice (control arm).

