### Sample size and power calculation

Lonsdale et al. [11] found a large difference in PA levels between free choice and structured PE lesson conditions (Cohen’s *d* = 1.07). We adopted a conservative approach and estimated a moderate effect size (medium *f* = 0.25) for mixed (between and within-subjects) analysis. Based on this estimation, as well as an estimated correlation of *r* = 0.5 among the repeated measures of PA (*r* = .53 in a previous study [11]), we required a sample of 76 students in order to achieve 95% power, with alpha set at .05. Taking into account the clustered nature of the data, this sample size was multiplied by a correction factor of 1+(*m* - 1)ρ, called the design effect, where *m* is the average cluster size and ρ is the intra-class correlation coefficient [35]. Assuming an *m* of 25 students per class and ρ = 0.1 (estimated based on a previous study [36]), the correction factor is 3.4. As a result, a sample of 258 students (i.e., 76 × 3.4 = 258) was required. To allow for lack of informed parental consent or assent from some students, and to protect against participant attrition across the four teaching conditions, we attempted to increase the sample by 20% and recruit 308 students from 16 PE classes.

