### Randomization

The 16 PE teachers, with their students, were randomly assigned to one of four conditions (three interventions and one control). An independent researcher, blinded to the study hypotheses, performed the allocation after the baseline assessment was administered. Randomization was conducted at the class-level and within schools to control for school characteristics, using a computerized random number generator with blocked randomization scheme (block size = 4). School 1 (Catholic – coeducational), School 2 (Independent – girls only), and School 3 (Independent – coeducational) each provided four classes of students and one class from each school was randomly assigned to one of the four conditions. School 4 and School 5 (two classes each) were both Catholic boys schools. Together, these two schools constituted the final block from which four classes were randomly assigned.

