### Planned statistical analysis

To assess the reliability of the teacher behavior ratings provided by the independent observers, intra-class correlation coefficients (ICCs) will be calculated. The fidelity of the interventions will be assessed using a MANOVA (with follow-up comparisons). If the manipulation of teacher strategies was successful, independent observer ratings of the intended strategy for each condition should be higher than ratings in other conditions. For example, ratings of choice should be higher in the two choice conditions than in any of the relevance and control conditions. To assess differences in primary and secondary outcome variables, linear mixed model analyses will be run on accelerometer counts, motivation and basic needs satisfaction, with students nested within teachers as a random effect. All analyses will be conducted based on the intention-to-treat principle.

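### Effects are framed as differences in change and no baseline adjustment is named; adjusting for the pre-randomization baseline would usually be more precise, by an amount that depends on an unstated class-level correlation

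*Protocol article*

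**What the plan says.** Hypotheses 1 to 6 in the protocol article are all comparisons of change against usual practice. The first expects the strategy lessons to "show greater increase in the percentage of time students spend in moderate-to-vigorous physical activity during PE lessons".

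Sample size and power calculation assumes a moderate effect "for mixed (between and within-subjects) analysis", with f = 0.25 and a correlation of 0.5 between the two activity measurements (0.53 in an earlier study). It concludes: "we required a sample of 76 students in order to achieve 95% power, with alpha set at .05". A design effect of 3.4 takes this to 258.

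Planned statistical analysis states that "linear mixed model analyses will be run on accelerometer counts, motivation and basic needs satisfaction", with students nested within teachers as a random effect. It does not say whether baseline enters as a covariate, as a repeated outcome or through a change score.

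The baseline is complete by design and precedes allocation. Methods/design reports: "Baseline and post-intervention data were collected from all participating students, regardless of study arm". Under Randomization, the independent researcher "performed the allocation after the baseline assessment was administered".

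**The concern.** Taken together, the hypotheses, the power basis and a mixed model without a named covariate point to an arm-by-time interaction. With two occasions and no constraint on the baseline means, that is a comparison of change scores.

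A change score subtracts the whole baseline, whatever the correlation. At r = 0.5 its variance equals that of the post-intervention value alone, so at student level the baseline buys no precision. A covariate analysis subtracts only the predictive part.

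This matters because there are four classes per arm. Precision is scarce, and chance baseline gaps between arms will be sizeable. Subtracting the full gap over-corrects for it.

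**Working it through.** **Inputs.** From Sample size and power calculation: f = 0.25, r = 0.5 (0.53 in the earlier study), α = 0.05, power 95%, N = 76, ICC ρ = 0.1, m = 25, design effect 3.4, total 258. From Randomization: 16 classes, four arms, four blocks. Assumed, because the article does not give it: the correlation c between a class's baseline and post-intervention effects, varied from 0 to 1. The 0.8 SD used for pairwise power is an illustration.

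**1. The plan's own figure.** For the within-between interaction with two occasions, λ = f²·N·2/(1 − r) = 0.0625·N·2/0.5 = 0.25N, on 3 and N − 4 df. The smallest N for 95% power is 73, or 76 in four equal groups (power 95.9%). The between-subjects test would need 210 and the within-subjects test 55, so 76 is the interaction, that is, the change-score test. Then 1 + 24 × 0.1 = 3.4 and 76 × 3.4 = 258.4. Both figures reproduce.

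**2. Student-level error variance.**
- Change score: 2(1 − r)σ² = 1.00σ² at r = 0.5; 0.94σ² at 0.53.
- Baseline as covariate: (1 − r²)σ² = 0.75σ² at 0.5; 0.72σ² at 0.53.
- Saving: 1 − (1 + r)/2 = 25% at 0.5; 23.5% at 0.53.

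**3. Class level, where randomization took place.** The variance of a class mean is V = ρ + (1 − ρ)/m. Holding total r at 0.5, the covariance of baseline and post class means is C = ρc + (0.5 − ρc)/m, and R = C/V. Change has variance 2(1 − R)V and the adjusted value (1 − R²)V, so the saving is (1 − R)/2.
- m = 16: V = 0.15625. R = 0.20, 0.50 and 0.80 at c = 0, 0.5 and 1. Saving 40%, 25% and 10%.
- m = 25: V = 0.136. R = 0.147, 0.50 and 0.853. Saving 43%, 25% and 7%.

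**4. Pairwise power for 0.8 SD, 258 students.** m = 258/16 = 16.1 and V = 0.1558. Residual class-level df: 16 − 1 − 3 (arms) − 3 (blocks) = 9 for change, and 8 with a class-mean covariate. At c = 0.5 the SE is √(2V/4) = 0.279 for change and 0.279 × √0.75 = 0.242 adjusted. Noncentral t, two-sided 5%:

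| c | R | Change, 9 df | Adjusted, 8 df |
|---|---|---|---|
| 0 | 0.20 | 52% | 73% |
| 0.5 | 0.50 | 72% | 83% (82.5%) |
| 0.75 | 0.65 | 86% | 91% |
| 1 | 0.80 | 98.0% | 98.6% |

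Variance removed by blocking is ignored in both columns.

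**5. Estimating the class-level slope.** Steps 3 and 4 treat the slope on the class mean as known. Estimated on 9 residual df, it multiplies the variance on average by 1 + 1/(9 − 2) = 8/7. The net variance ratio against change is then (1 + R)/2 × 8/7:
- R = 0.20: 0.69
- R = 0.50: 0.86
- R = 0.65: 0.94
- R = 0.80: 1.03

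Break-even is R = 0.75, or c of about 0.92 at m = 16. At c = 0.5 the SE becomes 0.242 × √(8/7) = 0.258, and power on 8 df about 77%.

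**6. Chance baseline gap.** Its SD between two arms is √(2V/4) = 0.28 SD. At R = 0.5 a gap of that size moves the change estimate by (1 − 0.5) × 0.28 = 0.14 SD.

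**The case against.** The strongest reply is that nothing here is an error. A hypothesis about greater increase is not a choice of model. Because allocation followed baseline, expected baselines are equal across arms, so a difference in change and a baseline-adjusted difference estimate the same effect. The planned model neither prescribes change scores nor excludes a covariate, and a condensed article may leave that to the analysis plan. Sizing on the interaction and then adjusting for baseline is common practice. All of this stands. A reader might infer that the trial is committed to change scores, that the hypotheses are misworded, or that 76 and 258 are wrong; the article supports none of these.

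A reader might also carry the 25% straight over to the treatment comparison. That would be too strong. The article's r is not stated to be a class-level correlation, and 25% holds for arms only if the class effects also correlate at 0.5. Nor is the 0.14 SD shift a bias of the design: it is conditional on a chance gap and averages to zero over randomizations.

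Finally, the class-mean covariate is not free with 16 classes. Step 5 shows that estimating its slope takes back part of the gain, and all of it if class means correlate above about 0.75. Using a student-level slope alone avoids that cost, but it can lose precision when class effects are very stable: at c = 0.9 and m = 25 its variance is 14% larger than that of the change score.

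What remains is that the article's only positive indications, the hypotheses and the power basis, point to the change comparison, and nothing in it points to adjustment.

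**Conclusion.** The point holds as a cheap gain in efficiency. The natural reading of the article is an arm-by-time comparison, which is valid but, over most of the plausible range, less precise than adjusting for the pre-randomization baseline.

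The size is 25% of the error variance at student level for r = 0.5. Between arms it is about 40% to 10% (16 students per class) or 43% to 7% (25 per class), under total r = 0.5, ICC 0.1 and a class-effect correlation from 0 to 1. In the middle case, pairwise power for 0.8 SD goes from about 72% to about 83% with the slope treated as known, and to about 77% with it estimated. If class means are very stable between the two lessons, the net gain is nil or slightly negative.

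**What to change.** Leave the hypotheses as they are. Under Planned statistical analysis, state that each student outcome's post-intervention value is modelled on arm, with the student's baseline value and the class-mean baseline as covariates, block as a fixed effect and teacher as a random effect. A repeated-measures model with arm means constrained equal at baseline is an acceptable alternative. Report the adjusted arm difference as the effect, and settle the choice before outcomes are examined by arm.

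No new data are needed. The cost is one sentence, about one class-level degree of freedom (9 to 8 in the blocked analysis), and the sampling error of the class-level slope shown in step 5. If the analysis plan already specifies such an adjustment, a reference to it in this section is enough.
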